### Outcome measures

The primary outcome is 90-day all-cause mortality. Secondary outcomes include ICU, hospital, 28-day and 180-day mortality rates and Sequential Organ Failure Assessment (SOFA) scores (on days 1, 3, 7, 14, 21 and 28). Tertiary outcomes include ICU and hospital LOS, hypoglycemia, hypokalemia, hypophosphatemia, hypomagnesemia, health care-associated infections
[26], refeeding syndrome
[27], and diarrhea
[28]. Definitions of different outcomes are outlined in Additional file
1: Appendix B. Hospital mortality is censored at one year from the date of enrollment. Vital status at day 90 and day 180 are recorded if needed by telephone interview with the patient or his/her surrogate decision maker.

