### Analytical plan

#### Sample size

In our recent RCT
[15], we observed an absolute risk reduction in hospital mortality of 8% (95% CI 0.4% to 25%). Based on an estimated 90-day mortality of 25% and using a power of 80% and an alpha of 0.05, the sample required to demonstrate a decrease in mortality of 8% was 431 in each group (a total of 862 patients). The flow of patients through the study will be displayed in a ‘CONSORT’ diagram (Figure
1). 

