#### Statistical and analytical plan

Patients will be analyzed according to the intention-to-treat principle, that is, all randomized patients will be analyzed in the groups to which they were originally allocated. Baseline characteristics will be summarized by carrying out univariate analyses. Categorical variables will be presented as numbers and percents, whereas the continuous variables will be presented as mean and standard deviations. The primary and secondary outcomes between the two intervention groups will be compared using the Chi-square test. The relative risk reduction, absolute risk reduction and the number needed to treat with the permissive underfeeding diet to prevent one death will be calculated. Moreover, the mechanical ventilation duration and ICU and hospital LOS in the two arms will be compared using the independent Student’s t-test. For binary outcomes, logistic multivariate regression will be used to test the intervention effect, controlling for covariates when appropriate, such as when analyzing subgroups. Adjusted relative risks and associated 95% CIs will be estimated using Cox proportional hazards regression modeling. Primary outcome will also be analyzed using survival analysis. All tests of significance will be at the 5% significance level, and two-sided. Analyses will be conducted using SAS version 9.2 and/or SPSS.

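### The plan takes adjusted relative risks from Cox regression, which on event times estimates a hazard ratio, not the relative risk of death by day 90

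*Protocol article*

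**What the plan says.** Under Outcome measures the protocol article states "The primary outcome is 90-day all-cause mortality", a risk at a fixed horizon. The Statistical and analytical plan then lists several analyses:

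- Unadjusted test: "The primary and secondary outcomes between the two intervention groups will be compared using the Chi-square test".
- Unadjusted effect measures: "The relative risk reduction, absolute risk reduction and the number needed to treat with the permissive underfeeding diet to prevent one death will be calculated".
- Covariate-adjusted testing: "For binary outcomes, logistic multivariate regression will be used to test the intervention effect, controlling for covariates when appropriate", with subgroup analysis given as an example.
- Adjusted effect measure: "Adjusted relative risks and associated 95% CIs will be estimated using Cox proportional hazards regression modeling".
- A further analysis: "Primary outcome will also be analyzed using survival analysis".

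The article does not say whether the Cox model behind the adjusted relative risks uses actual event times or a constant follow-up time.

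**The concern.** The label and the model do not match. A Cox model fitted to time to death estimates a ratio of hazards. The relative risk reduction planned in the same paragraph is built from the proportions dead at day 90. Under proportional hazards and a real effect, the hazard ratio lies further from 1 than the risk ratio, and the gap widens as mortality rises. Mortality in this population is not low: the design assumes 25%, and the Background reports 31.0% and 39.3% at 90 days in the team's previous trial.

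The trial report could therefore show two numbers under one name, a crude risk ratio and an adjusted hazard ratio, and readers would compare them directly. Anyone turning the adjusted figure into an absolute benefit would get the wrong answer. There is a known way to obtain a relative risk from Cox software, by giving every patient the same follow-up time, but its default standard error is wrong for binary data. Each default reading of the sentence thus has a defect, in either the label or the interval.

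**Working it through.** **Inputs.** The Sample size section gives control risk, power and alpha ("Based on an estimated 90-day mortality of 25% and using a power of 80% and an alpha of 0.05"), an absolute reduction of 8 points (so 17% v 25%) and 431 patients per group. The Statistical and analytical plan makes all tests two-sided at 5%.

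**The plan's own figure.** The usual two-proportion formula with pooled variance under the null gives 406 per group; with continuity correction it gives 431. The stated sample size reproduces, so 17% v 25% is the right design contrast.

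**Three measures at the design risks.**
- Risk ratio = 0.17/0.25 = 0.680, a 32.0% reduction. Number needed to treat = 1/0.08 = 12.5.
- Hazard ratio under proportional hazards = ln(1 − 0.17)/ln(1 − 0.25) = 0.648, so 1 − HR = 35.2%. Read as a relative risk, it implies a number needed to treat of 1/(0.25 × 0.352) = 11.4.
- Odds ratio = (0.17/0.83)/(0.25/0.75) = 0.614.

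On the log scale, ln(0.648)/ln(0.680) = 1.13, so the hazard ratio is 13% further from the null.

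**At other risks.** With the previous trial's 31.0% v 39.3%, the risk ratio is 0.789 and the hazard ratio ln(0.69)/ln(0.607) = 0.743: a 21% reduction would be read as 26%. Over assumed control risks of 17% to 42.5%, a risk ratio of 0.80 corresponds to a hazard ratio of 0.785 to 0.751, and a risk ratio of 0.90 to 0.891 to 0.871.

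**Timing of deaths.** Simulated data with 100,000 patients per arm and assumed death patterns gave:

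| Pattern (assumed) | Risk ratio | Cox, event times | Cox, constant time |
|---|---|---|---|
| Proportional hazards, 25% v 17% | 0.683 | 0.651 | 0.683 |
| Benefit before day 28 only | 0.686 | 0.648 | 0.686 |
| Benefit after day 28 only | 0.677 | 0.667 | 0.677 |
| Both arms 25% at day 90, deaths later in one arm | 0.988 | 0.931 | 0.988 |

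In the last row the true risk ratio is 1, and 0.988 reflects simulation noise. The hazard ratio of 0.931 reflects when deaths happen, not how many there are by day 90.

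**Constant-time Cox.** With Breslow handling of ties, the point estimate is the risk ratio. For the standard error of its logarithm, expected deaths are 431 × 0.17 = 73.27 and 431 × 0.25 = 107.75.
- Correct for binary data: sqrt(0.83/73.27 + 0.75/107.75) = 0.135.
- Model-based from constant-time Cox: sqrt(1/73.27 + 1/107.75) = 0.151.

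The ratio is 1.12, so the interval is about 12% too wide on the log scale. Around 0.68, the 95% interval would be 0.68 × exp(±1.96 × 0.1514) = 0.505 to 0.915, where 0.68 × exp(±1.96 × 0.1352) gives 0.522 to 0.886.

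**The case against.** The strongest defence is that the sentence may describe the constant-time method. Survival analysis of the primary outcome is listed separately and introduced as additional, which fits a first Cox model that is not a survival analysis. On that reading the estimate is a relative risk, the only harm is a conservative interval, and a robust variance is a detail that an article may leave to the full protocol. This stands in part. The text allows the reading but does not state it, and the model it does name yields a wrong interval by default. A stated analysis that is defective by default on both readings is more than an omitted detail.

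Several limits on the point also stand. At the design values the gap is ln(0.680) − ln(0.648), about 0.05, or roughly a third of the standard error of 0.135. A hazard ratio is a valid measure; the error lies in reading it as a risk ratio. The logistic model is planned for testing, and the article does not say that an odds ratio will be reported as the main effect.

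A reader might go further and infer that the reported relative risk will certainly overstate the effect, or that its failure to match the crude figure is itself a fault. The document supports neither inference. Overstatement requires a time-to-event fit, roughly proportional hazards and a non-null effect. A covariate-adjusted estimate may differ from the crude one under any model.

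**Conclusion.** The point holds as a mismatch between the named measure and the named model. If actual event times are used, the figure labelled an adjusted relative risk is a hazard ratio: 0.648 against 0.680 at the design risks, assuming proportional hazards. The gap is larger at higher mortality, smaller when benefit comes late, and absent under no effect with proportional hazards. If a constant follow-up time is used without a robust variance, the estimate is right and the interval is too wide. The article does not settle which applies. The consequence is confined to the adjusted effect estimate or its interval. The primary comparison and the crude effect measures do not depend on the Cox model, and the sample size reproduces as stated. The correction is worth making before the final analysis, but it does not threaten the primary conclusion.

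**What to change.** Replace the sentence on adjusted relative risks with one that names a model for risks at day 90. Options are modified Poisson regression with robust variance, log-binomial regression, or standardisation from the logistic model already planned. If constant-time Cox is intended, say so and specify a robust variance. Add that time-to-event Cox results will be reported as hazard ratios within the supportive survival analysis, and state which adjusted measure accompanies the primary outcome. The choice of covariates is a separate matter and need not change here.

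The cost is one or two sentences and standard regression procedures. No new data are needed, and the sample size and primary test stay as they are.

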#### Subgroup analyses

The following are *a priori* subgroups that will be analyzed: non-operative and operative patients, diabetic and non-diabetic patients, APACHE II ≤18 and >18, specific admission diagnoses (sepsis and traumatic brain injury), patients on vasopressors at baseline and those who are not and inclusion blood glucose (categorized according to the median value).

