### Randomization

PermiT is a multicenter open-label international RCT. The patients who meet all inclusion with no exclusion criteria are randomized into one of the two intervention arms: the permissive underfeeding group or target feeding group. Randomization is based on computer-generated random permuted blocks of four and is stratified by center and follows a concealed process using sealed and numbered envelopes that allocate the patient to either of the two arms of the study.

Patients may be randomized into PermiT only once unless they were discharged from the hospital and were re-admitted beyond 180 days of the first enrollment. The study does not allow cross-overs and if any occur, they will be reported as protocol violations.

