#### Blood glucose management

In both groups, the target blood glucose level is 4.4 to 10 mmol/L (80 to 180 mg/dL). Study centers may use their own insulin therapy protocols to achieve this blood glucose target.

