### Data collection, frequency and duration of follow-up following recruitment

At baseline for all randomized patients, data obtained include demographics, presence of co-morbidities such as chronic health problems, medication use prior to admission, Acute Physiology and Chronic Health Evaluation Scores (APACHE) II
[24] and III
[25] and presence of sepsis upon admission. Nutritional data (total calories and total protein), laboratory data (morning blood glucose, total insulin, hypoglycemic episodes, creatinine, potassium, magnesium and phosphorous), fluid input–output and stool frequency are recorded on a daily basis until a maximum of 14 days of ICU stay, ICU discharge or ICU mortality, whichever comes first. Data about healthcare-associated infections are also collected until two days after ICU discharge.

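### Inclusion blood glucose is examined as an effect modifier only by a split at the sample median, which loses information if the modification is smooth; a continuous treatment-by-glucose term should carry the test.

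*Protocol article*

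**What the plan says.** The Subgroup analyses section of the protocol article lists several a priori subgroups. One of them is "inclusion blood glucose (categorized according to the median value". No numeric cut is given for glucose, whereas APACHE II in the same list is divided at a fixed value of 18.

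The Statistical and analytical plan section provides logistic regression with covariates for binary outcomes and mentions subgroups in that connection. It describes no model with glucose as a continuous variable and no treatment-by-glucose interaction term. On testing it says "All tests of significance will be at the 5% significance level, and two-sided".

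Glucose appears in two other places. The data collection section names morning glucose among the daily laboratory data ("laboratory data (morning blood glucose, total insulin, hypoglycemic episodes, creatinine, potassium, magnesium and phosphorous"). The Blood glucose management section sets a treatment target: "In both groups, the target blood glucose level is 4.4 to 10 mmol/L (80 to 180 mg/dL".

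**The concern.** A median cut is a property of the sample that happens to be enrolled. Nobody can say in advance which patients will count as high, and another trial would draw the line elsewhere. Patients just either side of the line are treated as different in kind, while moderate and extreme values on the same side are pooled.

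If the effect of feeding on mortality changes gradually with glucose, a two-group comparison uses only part of the available information, and a real modification is more likely to be missed. What is at stake is the sensitivity and readability of this one subgroup analysis.

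**Working it through.** **1. The plan's own figure.** The Sample size section assumes 25% mortality at 90 days, 80% power and a 5% alpha, and gives the result as "the sample required to demonstrate a decrease in mortality of 8% was 431 in each group (a total of 862 patients". The test is two-sided, and allocation is equal (two arms, "computer-generated random permuted blocks of four and is stratified by center"). With 25% against 17% and a mean proportion of 0.21:

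- n = [1.960·√(2·0.21·0.79) + 0.842·√(0.25·0.75 + 0.17·0.83)]² / 0.08² = 405.7, or 406 per group without continuity correction.
- With the correction: (405.7/4)·[1 + √(1 + 4/(405.7·0.08))]² = 430.4, or 431 per group.

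The stated 431 per group (862 in total) is reproduced exactly. Nothing below depends on a fault in it.

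**2. Efficiency of a median split.** For a linear interaction, the information kept by replacing X with the indicator D = 1[X > median] is the squared correlation of X and D.

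- Normal X: cov = 1/√(2π) and var D = 1/4, so efficiency = (1/2π)/(1/4) = 2/π = 0.637. Loss 36%.
- Uniform X: cov = 1/8 and var X = 1/12, so efficiency = (1/64)/(1/48) = 0.75. Loss 25%.
- Log-normal X (simulated): 0.590 at log-SD 0.3, 0.557 at 0.4 and 0.517 at 0.5. Loss 41% to 48%.
- Exponential X (simulated): 0.480. Loss 52%.

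The article gives no glucose distribution, so these shapes are assumptions.

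**3. In patients and power, for the normal linear case.** 862 × 0.637 = 549, so the split carries the information of about 549 patients analysed continuously. An interaction test with 80% power on the continuous scale falls to Φ[(1.960 + 0.842)·√(2/π) − 1.960] = Φ(0.275) = 61%. One with 90% power falls to Φ[(1.960 + 1.282)·√(2/π) − 1.960] = Φ(0.626) = 73%.

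**4. Simulation at N = 862.** Model: logit p = −1.2 − 0.2t + 0.1e + 0.45·t·e, with t the arm and e either standardised glucose (linear truth) or ±1 either side of the median (step truth). There were 3,000 runs per scenario, with a Wald test of the interaction at two-sided 5%.

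| Truth | Glucose | Power, continuous linear term | Power, median split |
|---|---|---|---|
| linear | normal | 75% | 55% |
| linear | log-normal, log-SD 0.4 | 80% | 54% |
| step at median | normal | 56% | 76% |
| step at median | log-normal, log-SD 0.4 | 45% | 75% |

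The squared ratio of mean z, split to continuous, was 0.63 (normal) and 0.55 (log-normal) under the linear truth, in line with step 2. Under a step at the median the order reverses.

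**5. How large is the assumed interaction?** The design effect, 25% against 17%, is a log odds ratio of ln(0.17/0.83) − ln(0.25/0.75) = −0.487. An interaction of 0.45 per SD is nearly as large as that whole effect. With normal glucose, a linear truth and no treatment main effect (2,000 runs), power for continuous against split was:

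- 77% against 58% at 0.45 per SD;
- 29% against 19% at 0.225;
- 15% against 12% at 0.15.

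The absolute gain shrinks from 19 points to 10 and then to 3.

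**The case against.** The median rule is prespecified, is not chosen on outcome and gives strata of equal size. The median can be reported with the result, so readers can see where the line fell. The form of a subgroup model is often settled in a statistical analysis plan, and that plan is not shown. The information loss is conditional, and a linear term does worse if the truth is a step at the median. With a modest interaction neither analysis has useful power. All of this stands, and it limits the weight of the point. It does not remove it: the article fixes a particular method for this variable, and a better one is available within the regression already planned.

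A reader might infer more, in three directions that the document does not support.

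- *That the glucose value may be drawn after allocated feeding began, so that the strata depend on treatment.* The daily morning value is the only glucose measurement described in the data collection section, and glucose is not in the baseline list there. But the subgroup is defined by glucose at inclusion, which denotes an enrolment value. The baseline list is introduced as non-exhaustive, and it also omits operative status and baseline vasopressor use, both of which define subgroups. Nothing says that a post-allocation reading will be used, and a condensed article commonly leaves exact sampling time to the full protocol.
- *That the cut contradicts the 10 mmol/L limit.* That figure is the upper end of an on-treatment target, not a rule for classifying patients at baseline.
- *That the Background section treats glucose as a known effect modifier.* It remarks only that one cohort study did not adjust for glucose control, which is a point about confounding in that study.

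**Conclusion.** The point holds as a minor, worthwhile improvement to a stated method. As written, effect modification by inclusion glucose would be judged only through a cut that is unknown until enrolment ends and has no clinical anchor.

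The 36% figure assumes a roughly normal marker and a linear interaction. The 25% to 52% range rests on the assumed shapes above. A step at the median removes the loss altogether, so it should not be reported as an unconditional loss of a third. The 20-point power difference in the first row of the table likewise belongs to an interaction almost as large as the trial's whole design effect, and should not be read as the expected gain.

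The consequence is limited to one secondary subgroup analysis. The primary 90-day mortality comparison and the sample size stand.

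**What to change.** In the Subgroup analyses section, make the primary test for this subgroup a treatment-by-glucose interaction in the logistic model, with inclusion glucose as a continuous term. Use a linear term, or a restricted cubic spline to allow for non-linearity, and state which before the final analysis. Say in the same sentence that inclusion glucose means the value before randomization; this makes the evident intention explicit. Keep the median split, or a few fixed prespecified glucose values, for display only.

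The cost is a wording change and one extra model, with no change to enrolment, treatment or sample size. The drawback is that a fitted curve is slightly harder to place in a forest plot than two rows, which the retained display split answers.

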### Monitoring for safety

Several measures are taken to minimize, observe and document any potential safety concerns. First, serious adverse events (SAEs) will be reported immediately to the Steering Committee, IRB and DMC. Second, an independent DMC will be monitoring the safety of the trial. Third, one interim analysis has been conducted, and the next one will be done once 2/3 of the total sample size is recruited. Finally, site visits to the participating centers by the principal investigator or designee are planned for data monitoring including data verification and review of the consent process.

## Discussion and Trial status

This trial was designed in 2008. The protocol passed through multiple amendments. Final approval from IRB was obtained on 8 April 2009. The study began enrolling at the principal site in November 2009. It was subsequently joined by one national (King Faisal Specialist Hospital and Research Center) and three international centers (Ottawa Hospital, General Campus, the Ottawa Hospital, Civic Campus and Mount Sinai Hospital in Toronto). The expected duration of the study is four years. The first DMC meeting was held on 7 October 2009 and a follow-up meeting on 9 February 2011. The study monitor visited the coordinating site on 7 January 2012 and submitted a detailed report to the sponsor. The first interim analysis was carried out in March 2012 as soon as 287 patients (one-third of the sample size) were completed with 90-day outcome. Unblinded results were submitted to the DMC, who indicated that trial recruitment should proceed. The results were maintained blinded to the investigators/research team with the exception of the biostatistician.

## Abbreviations

ACCEPT: Algorithms for Critical-Care Enteral and Parenteral Therapy; APACHE: Acute Physiology and Chronic Health Evaluation; ASPEN: American Society for Parenteral and Enteral Nutrition; BMI: body mass index; DMC: Data Monitoring Committee; ICH-GCP: International Conference on Harmonization-Good Clinical Practice guidelines; IRB: Institutional Review Board; KAIMRC: King Abdullah International Medical Research Center; KSAUHS: King Saud bin Abdulaziz University for Health Sciences; LOS: Length of Stay; PN: Parental Nutrition; RCT: Randomized Control Trial; SCCM: Society of Critical Care Medicine.

